### Procedure

Before teams are randomised, all managers will be given information sheets and asked to sign a consent form providing permission for their team to be involved in the trial. We will collect demographic information about the EIP teams to create a list of eligible service users and a cross-coding sheet by which each service user can be allocated an anonymous trial ID. Demographic information will include team location, number of care co-ordinators within the team, size of caseloads and distance to dental services from the team base. The trial team will not have access to identifiable NHS data.

#### Dental intervention

After randomisation, EIP teams allocated to receive the dental intervention will be approached by the trial team to arrange a convenient time to conduct the one-off dental awareness training at the start of the 12-month intervention period. Information sheets will be given out to care co-ordinators and consent forms will be signed. This will fit within the usual multidisciplinary team meetings, but is likely to take around 30 minutes, including time for questions and shared experiences. There will be a manual in order to keep it consistent for all teams (see Additional file 2). The training will briefly cover the aims and background of the trial, how to complete the checklist, service user ID number allocation, how to return the completed checklists to the trial team and discussion about what to do in certain situations regarding adverse events. The care co-ordinators will be encouraged to use the checklist for all their service users at their earliest convenience. The checklist is printed on carbonless copy paper, one copy of the dental checklist will be kept in the service users’ notes and one will be returned in pre-paid envelopes to the trial team. Care co-ordinators will also be encouraged to offer their service users an oral hygiene information sheet which contains oral hygiene tips and information on how to find an NHS dentist (see Additional file 3).

#### Control group

EIP teams allocated to the control group will continue to deliver standard care for 12 months. They will receive the dental awareness training and will be asked to use the dental checklist one year after the intervention group, following the same procedure as the intervention group. Care co-ordinators in control teams will be given information sheets and asked to sign consent forms.

#### Follow-up

The trial team will prompt the intervention group care co-ordinators for the 12-month follow-up where dental checklists will be completed again for all service users. A total of 100 service users will be randomly selected from all teams and their care co-ordinators will be encouraged to ask them if contact from the trial team is acceptable regarding the Oral Impacts on Daily Performance (OIDP) measure as well as for collecting detailed data from their dentists (if they have visited a dentist within the previous 12 months). If it is not - no contact will be made. For this person, the trial is then over. The OIDP is a scale which assesses the impacts to which dental problems affect an individual’s life on a daily basis (see Additional file 4).

All service users who have indicated that contact from the trial team is acceptable will be contacted by an independent researcher and consent gained for conduct. For the OIDP information sheets will be given out and consent forms will be signed. The OIDP will then be administered as a short 20-minute interview by the researcher. For the detailed dental data, information sheets will be given out and consent forms will be signed. Dentists will then be contacted and information about recent dental treatment and current state will be requested Figure 1.

**Figure 1 F1:**
[figure not shown]
CONSORT flow diagram of participants through the trial.

### Serious unexpected events

Adverse events due to participating in this trial are not expected. Service users’ mental health will be closely monitored by their EIP teams, care co-ordinators will be asked to inform the trial team of any adverse event that either the care co-ordinator or service user feels was due to the checklist. The trial team will determine the seriousness and causality in conjunction with any treating medical practitioners. Serious adverse events are divided into two categories, those that seem likely to be independent of an oral checklist and those connected to oral healthcare. All adverse events will be recorded and closely monitored until resolution, stabilisation, or until it has been shown that involvement in the trial is not the cause by the data monitoring committee. All treatment-related serious adverse events will be recorded and reported to the REC as part of the annual reports. Unexpected serious adverse events will be reported to the REC by the chief investigator who will take appropriate medical action, which may include halting the trial and informing the sponsor of such action. If the event is determined to be due to involvement in the trial the REC will be informed using the reporting form found on the NRES web page within seven days of knowledge of the event. Within a further eight days, the trial team will send any follow-up information and reports to the REC. Any necessary amendments to the protocol will be made and the REC will be informed as required. Any participant who experiences an adverse event may be withdrawn from the study at the discretion of the investigator.

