#### Governance

The Advisory Group is a multidisciplinary group to give advice and direction to the overall project and will meet every six weeks to begin with but will also provide continuing support and meet every few months for the duration of the trial. The Steering Group will meet twice a year to monitor the overall progress of the trial, adherence to the protocol and patient safety. The Data Monitoring Group will meet once a year to assess the progress and safety of the trial while providing the sponsor with recommendations regarding trial modification, continuation or termination. The Management Group consists of the trial team and will meet every week regarding the day-to-day running of the trial and data collection. This group will also communicate any unexpected events to both the Steering Group and the Advisory Group.

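### Adverse events are reported only if someone attributes them to the checklist, which control teams do not use in the comparison year, so adverse-event reports cannot be compared between arms

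*Protocol article*

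**What the plan says.** The section Serious unexpected events describes one route by which an adverse event reaches the trial team: "care co-ordinators will be asked to inform the trial team of any adverse event that either the care co-ordinator or service user feels was due". The cause named there is the checklist. The trial team then judges seriousness and causality together with any treating practitioners. The same section says that every adverse event is to be recorded and followed, and it adds: "Serious adverse events are divided into two categories, those that seem likely to be independent of an oral checklist and those connected to oral healthcare".

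The section Dental intervention places the "one-off dental awareness training at the start of the 12-month intervention period", and lists among the topics of that session "discussion about what to do in certain situations regarding adverse events". For the other arm, the section Control group says "EIP teams allocated to the control group will continue to deliver standard care for 12 months", and then: "They will receive the dental awareness training and will be asked to use the dental checklist one year after the intervention group". Control co-ordinators also receive information sheets and consent forms; the article does not state what these say about adverse events.

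Under Secondary outcomes, the article lists whether service users left the service for any reason, including death, without limiting this to one arm. Under Governance, "The Data Monitoring Group will meet once a year to assess the progress and safety of the trial" and advises the sponsor on modifying, continuing or stopping the trial.

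**The concern.** The trigger makes a causal judgement the condition for reporting, and it names one component of the intervention as the cause. Control service users have no checklist in the comparison year, so nothing that happens to them can qualify. In the intervention arm, the judgement that decides whether an event is seen at all is made by a co-ordinator or service user in an open trial, before the trial team assesses causality.

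Two things are at stake. First, any count of adverse-event reports by arm would reflect the reporting rule: a few reports in one arm against none in the other would not show harm, and none in both would not show safety. Second, harm that nobody links to the checklist would not be reported by this route, even if another part of the intervention caused it.

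**Working it through.** The article gives no adverse-event rate and no safety sample size, so there is no planned figure to reproduce. The check traces the rule by arm and against the rest of the text.

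**1. Reports by arm in the comparison year**

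| | Intervention teams | Control teams |
|---|---|---|
| Checklist in use | Yes | No, one year later |
| Training session that covers adverse events | At the start | One year later |
| Event that could be attributed to the checklist | Possible | Not possible |
| Reports under the trigger | True events × share blamed on the checklist | 0, whatever the true rate |

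The control zero follows from the missing checklist alone. It does not depend on when control co-ordinators are told about adverse events.

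**2. Illustration of the size**

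Expected intervention reports = n × true event rate × share blamed on the checklist.

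- From Trial status: 1,074 service users in the 10 randomised teams. Assuming an even split, n = 1,074 / 2 = 537 per arm.
- Assumed, not in the article: a true event rate of 1% to 10%, the same in both arms, and 5% to 25% of intervention-arm events blamed on the checklist.
- Low end: 537 × 0.01 × 0.05 = 0.27, about 0.3 reports.
- High end: 537 × 0.10 × 0.25 = 13.4, about 13 reports.
- Control arm: 537 × 0.01 = 5.4 to 537 × 0.10 = 53.7 true events, and 0 reports.

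The true rates are equal throughout, so the whole difference in reports comes from the rule.

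**3. The trigger against the intervention**

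Health economic analysis describes the intervention as training, an information sheet and a checklist, and expects more dental appointments in intervention teams. Ethical considerations says that the combined intervention will influence service users who never complete a checklist. A trigger tied to the checklist is therefore narrower than the intervention being tested.

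**4. The safety section against itself**

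- It promises to record all adverse events but asks only for those blamed on the checklist. The two agree only if all events means all events reported.
- One serious-event category is for events independent of the checklist. Under the trigger it can hold only reports that someone blamed on the checklist and the trial team later judged unrelated.
- The two categories do not cover all cases. A psychiatric serious event thought to be due to the checklist is neither independent of it nor connected to oral healthcare, although the section says that mental health is what the teams will monitor closely.
- The suspected cause changes through the section: trial participation, the checklist, oral healthcare, treatment. These are not the same thing.

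**5. Other safety information**

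Death and leaving the service are listed for service users generally. The sample of 100 for the oral-impacts interview is drawn from all teams. Neither is linked in the text to adverse-event reporting or to the Data Monitoring Group.

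**The case against.** The strongest reply is proportionality. The intervention is a staff session, a checklist and an information sheet within routine care. The article expects no adverse events from participation, lists no adverse-event outcome among its primary and secondary outcomes, and promises no between-arm comparison of adverse events. Reporting based on attribution can be a reasonable choice for such a trial. This stands as a limit on the severity of the point. It does not make the rule fit the promise to record all adverse events, or a group charged with assessing safety.

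Three stronger readings are tempting, and the article does not support them.

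- *No between-arm safety comparison of any kind is possible.* Death and leaving the service are not restricted to one arm, and the interview sample covers all teams. The limit applies to adverse-event reports.
- *Instructions on adverse events are given only in the training.* The training is the only place where the article describes them, but the content of the control information sheets, the training manual and the full protocol is not shown.
- *The category of events independent of the checklist must stay empty.* The reporter's belief opens the route and the trial team decides causality afterwards, so reclassified reports can fill it.

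It is also fair to say that the article does not state what data the Data Monitoring Group receives, and that reporting to the ethics committee turns on involvement in the trial, a wider term than the checklist. Both points soften the consequence. Neither brings in an event that was never reported.

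**Conclusion.** The point holds for adverse-event reports. Read literally, the trigger yields no control reports in the comparison year, so a between-arm contrast of these reports has no meaning. It also leaves out harm through the rest of the intervention unless someone blames the checklist, and it fits poorly with the section's promise to record all events and with its two serious-event categories.

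The control zero rests only on the stated trigger and on the stated delay of the checklist. The range of about 0.3 to 13 intervention reports against 0 is an illustration. Its rates and blame shares are assumptions, the even split is assumed, and 1,074 is the teams' total caseload, which may exceed the number eligible because under-18s and people unable to consent are excluded.

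This should be corrected, but it is a modest defect: the intervention is low risk, and the objective concerns oral health behaviour, which the point does not touch.

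**What to change.** In Serious unexpected events:

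1. Reconcile the reporting trigger with the statement that all adverse events are recorded.
2. Define both the trigger and relatedness by one referent: any part of the intervention, or trial participation. Record event type (dental, psychiatric, other) as a separate item in place of the two serious-event categories.
3. Give control co-ordinators the same reporting instruction when they consent, without the dental training.
4. Give the Data Monitoring Group by-arm counts of the death and leaving-service data already listed as outcomes, over the same 12 months from randomisation in both arms.

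If the sponsor prefers to keep the present trigger, the protocol should state that adverse-event reports are based on attribution and cannot support a between-arm safety conclusion.

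Collecting further events whatever their cause, such as admissions or urgent dental attendance, is optional. The documents do not show that the teams hold those records, and service users agree only to answer the checklist.

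The cost is a wording amendment, with ethics and R&D opinion where the article's own rules require it, and a few minutes of co-ordinator time. Follow-up describes a 12-month prompt only for intervention co-ordinators, so the amendment should also say how the control teams' death and leaving data are returned.

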### Outcomes

#### Primary outcomes

Number of service users who have visited a dentist within 12 months of exposure to the checklist as reported on the checklist.

#### Secondary outcomes

Registered with a dentist, routine check-up within the last 12 months, owning a toothbrush, cleaning teeth twice a day, non-routine visit to a dentist in the last year, replacing existing toothbrush within the last six months, problems with mouth and teeth, OIDP. A cost analysis will also be carried out and other outcomes will include whether any service users have left the EIP service for any reason, including whether they refused to give consent, were discharged to another service, or whether they passed away.

### Data

#### Data analysis

This is a cluster randomised controlled trial with a small number of clusters but many participants within the clusters. We anticipate 600 to 800 dental checklists to be completed during the trial. The analysis will focus on whether the intervention has made a clinically significant difference to the data collected from the intervention teams (Additional file 5). The expected analysis will be a multilevel modelling or random effects methods. We will not analyse any difference between the care co-ordinators. . Data will be entered into a password-protected database with an audit trail.

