**Methods/Design:**

This is the protocol for a pragmatic cluster randomised trial that has been designed to fit within standard care. Dental awareness training for care co-ordinators plus a dental checklist for service users in addition to standard care will be compared with standard care alone for people with mental illness. The checklist consists of questions about service users’ current oral health routine and condition. Ten Early Intervention in Psychosis (EIP) teams in Nottinghamshire, Derbyshire and Lincolnshire will be cluster randomised (five to intervention and five to standard care) in blocks accounting for location and size of caseload. The oral health of the service users will be monitored for one year after randomisation.

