## Methods

### Randomisation

This is a pragmatic, open, cluster randomised controlled trial. We are limited by the number and size of the teams as well as by the compliance of the care co-ordinators. The Nottingham Clinical Trials Unit (CTU) will create a randomisation program that will be used by the researcher to randomise the EIP teams. The researcher will list the teams in such a way as to anonymise them, we will then block randomise; the block being the number of teams within each county. This will ensure that each county gets some degree of exposure to the intervention. EIP teams will be grouped into pairs according to location and size of team, which will then be randomised with one team being allocated the active intervention and the other the control. Randomisation will be stratified to ensure that both of the interventions are roughly equal in terms of team location, number of care co-ordinators within the team and size of caseloads. The CTU will keep full records of the procedure, but there will be no requirement for having procedures for breaking code.

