## Trial status

Recruitment started in February 2012. As of August 2012, 10 EIP teams caring for a total of 1,074 service users have been randomised. Recruitment for new trial sites is underway.

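### The random-effects analysis of ten teams fixes no small-sample inference; uncorrected, a nominal 5% test would reject a true null about 6–13% of the time if pairing is uninformative

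*Protocol article*

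**What the plan says.** The Data analysis section describes the study as having "a small number of clusters but many participants within the clusters" and continues: "The expected analysis will be a multilevel modelling or random effects methods". It gives no estimator, reference distribution or small-sample correction, and it does not say whether county or pair enters the model. It refers to Additional file 5, which is not shown.

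The Abstract gives ten teams, five per arm. Trial status reports that "10 EIP teams caring for a total of 1,074 service users have been randomised", and also that "Recruitment for new trial sites is underway".

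On restriction, the Randomisation section says "we will then block randomise; the block being the number of teams within each county", and then "EIP teams will be grouped into pairs according to location and size of team", with one team of each pair going to each arm.

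The Sample size section sets alpha at 0.05. The Health economic analysis section makes a full economic evaluation conditional on a statistically significant difference between the arms, and otherwise plans only a cost analysis.

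**The concern.** The team is the unit of randomisation, so evidence about the intervention comes from ten team-level results, however many service users each team contributes. The usual large-sample output of a random-effects model treats the between-team variance as well estimated and uses a normal or chi-squared reference. With ten teams neither holds. Maximum likelihood tends to underestimate the between-team variance, and the reference should be a t distribution with at most 8 degrees of freedom.

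The section notices that clusters are few but draws no consequence for the inference. If default output were used, the p-value would be too small and the confidence interval too narrow. Because significance decides whether the full economic evaluation goes ahead, a false positive would have a further effect inside the trial.

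**Working it through.** **Inputs from the protocol.** Ten teams, five per arm; two-sided 0.05 (this reproduces Table 1); ICC guess 0.1; control attendance 5% to 35% in Table 1; 600 to 800 checklists, so 60 to 80 per team if all ten contribute. The sample size of 334 before dropout gives 334/10 ≈ 33 per team.

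**The plan's own figures.** For 5% against 20%, the continuity-corrected two-proportion formula gives 176; 176 × 1.9 = 334.4, stated as 334; 334/0.8 = 417.5, stated as 418. The non-cluster N matches in all seven rows. The document states no type I error other than the nominal 0.05.

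**Normal theory, ten team means, no pair or county term.** Degrees of freedom = 10 − 2 = 8.

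- REML with z: P(|t8| > 1.96) = 8.6%.
- ML with z: the ML variance is 8/10 of the unbiased one, so the test rejects when |t8| > 1.96 × √(8/10) = 1.753; P = 11.8%.
- Likelihood ratio: reject when 10·ln(1 + t²/8) > 3.84, that is |t8| > 1.936; P = 8.9%.

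**Simulated null trials, ML random-intercept logistic model, no pair term.** In the first table the ICC is on the latent (logit) scale, with 2,000 trials per row, team-size coefficient of variation 0.3 and allocation within five pairs. Shared is the proportion of team variance common to a pair. Entries are rejection percentages at nominal 5%.

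| ICC | Users per team | Attendance | Shared | Wald z | Likelihood ratio | Wald, t8 | Team t-test, 8 df | Paired t, 4 df |
|---|---|---|---|---|---|---|---|---|
| 0.10 | 70 | 30% | 0 | 10.7 | 8.5 | 6.2 | 4.6 | 5.0 |
| 0.05 | 70 | 30% | 0 | 11.4 | 9.0 | 7.1 | 5.1 | 5.0 |
| 0.02 | 70 | 30% | 0 | 9.2 | 7.6 | 5.4 | 5.0 | 5.0 |
| 0.01 | 70 | 30% | 0 | 7.5 | 6.3 | 3.8 | 5.0 | 4.6 |
| 0.10 | 33 | 10% | 0 | 9.5 | 8.0 | 5.1 | 4.6 | 5.0 |
| 0.05 | 70 | 30% | 30% | 6.7 | 5.3 | 4.1 | 2.8 | 4.6 |
| 0.05 | 70 | 30% | 50% | 5.6 | 4.2 | 2.9 | 2.0 | 4.6 |

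The design effect in the Sample size section is applied to proportions, so the ICC was also taken on the proportion scale (beta-distributed team rates, 20% attendance, no pair correlation, 3,000 trials per row):

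| ICC | Users per team | Wald z | Likelihood ratio | Team t-test, 8 df |
|---|---|---|---|---|
| 0.10 | 60 | 13.5 | 9.5 | 5.2 |
| 0.05 | 70 | 11.5 | 8.7 | 4.9 |
| 0.02 | 70 | 10.0 | 8.1 | 4.8 |

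In this second set, an ML fit with t8 in place of z still rejected 5.8–8.7%. Monte Carlo standard errors are at most about 0.7 points in both sets.

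**Interval width.** 2.306/1.96 = 1.18, so 18% wider at the same standard error. Against an ML fit whose standard error is also too small, normal theory gives 2.306/1.753 = 1.32.

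**If restriction terms are added.** Three counties leave 8 − 2 = 6 degrees of freedom and five pairs leave 5 − 1 = 4. By the same normal theory, using z with 4 degrees of freedom would reject 12.2% (REML type) or 28% (ML type).

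**The case against.** The strongest objection is that the section calls this the expected analysis and never mentions z inference. A condensed article commonly leaves estimator, degrees of freedom and covariates to a statistical analysis plan, and a mixed model with small-sample degrees of freedom falls within the named class. That stands, and it limits the point: the plan cannot be said to have a wrong error rate. It does not remove the point, because the section itself raises the small number of clusters and then names a family of methods whose default inference fails there.

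Four stronger readings are tempting, and the document does not support them.

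- *The true type I error is 10–13%.* That is one case: ML, Wald z, moderate ICC, uninformative pairs. The likelihood-ratio test and REML with z stay below 10%.
- *The analysis ignores the pairs and county blocks, which makes matters worse.* The text does not say that they are left out. Leaving out informative pairs makes the test more conservative, so the two effects offset each other.
- *The Randomisation section gives two contradictory schemes.* Size-matched pairs inside county blocks is a compatible reading. The wording is loose but is not shown to be wrong.
- *With five pairs no result could reach p < 0.05.* The floor of 2/32 = 0.0625 belongs to a two-sided permutation test, and none is planned.

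Further sites may also join, which would raise the degrees of freedom and shrink the excess.

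**Conclusion.** The point holds as a gap in the stated analysis. With ten teams and pairing that carries no information, uncorrected large-sample inference rejects a true null about 6–13% of the time at nominal 5%. Where in that range depends on estimator, ICC and the scale on which the ICC is defined. If pairs are informative and left out, Wald z comes down to about 6–7% (5.6–6.7% at ICC 0.05). A team-level t-test on 8 degrees of freedom stays at 4.6–5.2% without pair correlation and is conservative with it (2.0–2.8%).

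These figures assume ten teams. Apart from the protocol's ICC guess of 0.1, the simulated ICCs, team-size variation and pair correlations are assumptions; attendance lies within the range of Table 1. The REML figure is from normal theory and was not simulated.

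**What to change.** In Data analysis, name the primary test as one of:

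- a comparison of team-level attendance proportions on between-team degrees of freedom (8 for ten teams, critical value 2.31), updated if teams are added; or
- a mixed model with a team random effect and a small-sample correction shown to hold the 5% level at this number of teams. Replacing z by t8 after an ML fit is not fully sufficient.

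The team-level comparison is the simpler and safer of the two.

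If county or pair terms are included, reduce the degrees of freedom to match. Including pairs is a design choice and is not required here. A paired comparison held 4.6–5.0% in every scenario, but five pairs leave 4 degrees of freedom and a critical value of 2.78; the unpaired test gives up some power if the pairs are informative.

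In Randomisation, state how county blocks and pairs were combined. This is a clarification, and since ten teams are already allocated it is a matter of record.

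The cost is wording, an interval about 18% wider at the same standard error, and somewhat lower power.
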